### Study status

The study started recruitment in September 2025, and enrolment is currently ongoing.

## Discussion

Long-acting injectable cabotegravir (CAB-LA) has recently been recommended by the WHO as an additional HIV prevention option for individuals at a substantial risk of infection, supported by strong efficacy and safety data from randomised trials.
^
21
^ Despite this progress, WHO highlights a critical evidence gap regarding the safety, pharmacokinetics, and programmatic implications of CAB-LA use during pregnancy and breastfeeding (two periods associated with heightened HIV susceptibility and the potential risk of vertical transmission.
^
7
^ In response, Malawi endorsed the introduction of the CAB-LA through a national implementation science platform that explicitly included lactating women as an important subpopulation requiring targeted evidence.
^
22,
23
^

To our knowledge, the CABMILK study is the first to leverage this national CAB-LA rollout platform to systematically characterise cabotegravir exposure in lactating mothers initiating injectable postpartum PrEP. By measuring cabotegravir concentrations in both maternal plasma and breast milk after achieving a steady state (i.e. after five injections,
^
16
^ this study will quantify the extent and pattern of transfer into breast milk across the dosing interval). Subsequent measurement of cabotegravir concentrations in breastfed infants will allow us to determine the degree of infant exposure and the pharmacokinetic relationship between the maternal blood, milk, and infant compartments.

This work addresses a fundamental pharmacological question: whether cabotegravir, given its hydrophobicity
^
9
^ and high protein binding,
^
10
^ exhibits minimal excretion into breast milk, as predicted. Or whether measurable transfer occurs, similar to reports for other integrase inhibitors such as dolutegravir.
^
12,
13
^ If cabotegravir is detectable in infant plasma, we will assess whether concentrations approach thresholds associated with antiviral activity or selection pressure, thereby revealing the potential risk of resistance emergence.

In addition to pharmacokinetic outcomes, CABMILK provides a unique opportunity to compare infant growth, morbidity, and early developmental milestones among infants in three exposure groups: CAB-LA, oral PrEP (TDF/FTC), and PrEP-naïve groups. Using caregiver-reported developmental indices complemented by routine clinical assessments, the study will generate population-level comparative data on infant wellbeing during the follow-up period. These findings will contribute essential early safety signals and support national and global guidance on the use of long-acting PrEP in breastfeeding populations.

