### Step 2-
Cabotegravir safety, growth pattern and development study

We hypothesise that there will be no difference in the incidence of adverse events or illnesses, growth, and development between infants exposed to breast milk CAB and those exposed to breast milk oral PrEP. 25 mother-infant pairs from Step 1 (mothers receiving CAB for PrEP), 25 other mother-infant pairs from the oral PrEP group of the PathToScale and LINK studies and 50 mother-infant pairs naïve of PrEP, matched to those in the CAB PrEP group, will be followed up for eight months from the time of maternal PrEP initiation in the PrEP groups or a similar time in the PrEP naïve group. The PathToScale and LINK studies are following up mothers in the CAB group from the initiation visit, 1 month later and, thereafter, every 2 months. In our study we will follow a similar schedule for all three groups with a final exit visit scheduled at eight months post initial CAB dose. This will result in 10 scheduled visits in the CAB group and six in the oral PrEP and no PrEP groups. The CAB LA PrEP group will have four additional visits for PK sampling at month 7. In the present CABMILK Study, we will utilise all six planned visits to assess the incidence of reported adverse events and infant growth by measuring anthropometric indices (weight-for-height and height-for-age) as well as head circumference-for-age. The same visit schedule and safety assessments will be applied to the oral PrEP and PrEP-naïve groups. Infant growth and neurodevelopment will be longitudinally assessed at all six study visits using the Caregiver Reported Early Development Instrument (CREDI).

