### Sample size determination and power calculation

Sample size calculation has been primarily based on step 1 of the CABMILK study. Step 2 leverages on the previous step. In Step 1 (Cabotegravir maternal, breastmilk and infant pharmacokinetic study), previous data on 600 mg intramuscular CAB in adults yielded an area under the concentration-time curve (AUC0-∞, μg*h/mL, [range]) of 4172 [2839–6597] with a coefficient of variation of 24%.
^17^ Assuming a similar coefficient of variation, the inclusion of 25 breastfeeding infants will provide >95% precision to estimate overall infant CAB exposure.

Step 2 (Prospective observational cohort follow-up of mother–infant pairs): Detecting rare safety outcomes or subtle neurodevelopmental effects related to cabotegravir exposure would require substantially larger and longer-term studies. Accordingly, Step 2 is designed as a prospective observational cohort to describe infant exposure and characterise safety signals rather than to support formal inferential comparisons. Safety outcomes will include reported adverse events, growth patterns, and changes in developmental status over time.

We plan to enrol 100 mother–infant pairs (25 CAB-LA, 25 oral TDF/FTC PrEP, and 50 PrEP-naïve). This sample size is intended to provide a reasonable descriptive profile of safety and developmental outcomes across exposure groups. The larger PrEP-naïve group will support more stable estimation of background patterns against which findings in the exposed groups can be contextualised.

Child development will be assessed using the CREDI Short Form, a caregiver-reported tool that provides a summary developmental status score suitable for population-level description rather than clinical diagnosis. Assessments over 8 months of follow-up will allow characterisation of short-term developmental trajectories, while recognising that longer-term outcomes cannot be determined within this study.

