### Data analysis

Data will be analysed using either STATA or R.
Table 2 outlines the planned data analyses stratified by the specific objectives of the study. Infant age at every sampling occasion and at every safety and developmental assessment will be recorded to the day. Both postnatal age (PNA) and postmenstrual age (PMA = gestational age at birth + PNA) will be derived for each timepoint and treated as time-varying variables. The population pharmacokinetic model (NONMEM/Monolix) will incorporate, as fixed structural features, allometric size scaling (exponent 0.75 on apparent clearance, 1 on volume of distribution) and a sigmoidal maturation function on apparent clearance, with PMA50 and the Hill coefficient set to published values for UGT1A1 ontogeny rather than estimated from this small cohort. Residual covariate effects of PNA, weight, sex, and feeding pattern will then be tested empirically. To probe the robustness of the maturation assumption, we will conduct a pre-specified sensitivity analysis re-fitting the model with at least one alternative published UGT1A1 ontogeny parameter set (1) and report the resulting impact on individual exposure estimates. Relative infant dose (RID) will be reported overall and by infant-age stratum (<9 months and 9–<12 months). Comparative growth and developmental analyses will use WHO z-scores and age-adjusted CREDI scores; longitudinal mixed-effects models will include infant age at measurement as a continuous covariate. Because exposure groups are self-selected, all comparative analyses are observational and exploratory. Primary safety results will be descriptive: counts, proportions with exact 95% confidence intervals, incidence rates, and Kaplan–Meier curves, without group-comparison p-values. Longitudinal growth and CREDI outcomes will be analysed with mixed-effects models adjusting for a minimal pre-specified set of covariates: infant age at measurement, infant sex, and site. Formal between-group inference for safety is deferred to other larger PK studies. Where feasible, we will perform sensitivity analyses to reduce imbalance, recognising limitations due to our sample size.

**Table 2. T2:** Planned data analyses aligned with study objectives in the CABMILK study.

Objective	Data analysis	Outcome

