To profile the extent of CAB transfer in breast milk and determine its pharmacokinetics in infants whose mothers receive long-acting injectable cabotegravir for HIV preexposure prophylaxis (PrEP).	We will use non-linear mixed effects models to determine the compartmental pharmacokinetics of CAB from maternal plasma to breast milk to infant plasma. We will first calculate the milk: plasma ratio to determine the average milk CAB concentration compared with the average maternal plasma concentration. Second, we will utilise individual predicted infant CAB concentrations to calculate infant overall exposure (AUC0-∞) and estimate CAB infant half-life as well as elimination rate constant. Third, we will estimate the CAB dose ingested by each infant, through breast milk, relative to the maternal dose; the relative infant dose (RID). ^ 25 ^ This RID will allow us to determine the extent of CAB breast milk exposure that would result in attained concentrations in the infant’s blood that are above or below the protein-adjusted IC90 of 0.166 μg/mL. ^ 26 ^	CAB transfer to the infant through breast milk, and profile the attained infant concentrations.
To determine the association of breast milk CAB exposure and infant safety outcomes (growth pattern, neuro-cognitive development, and incidence of adverse events).	Firstly, mean anthropometric indices (weight-for-height, height-for-age, head circumference-for-age) will be compared across three groups using independent t-tests. Secondly, adverse events (overall morbidity) by the end of follow-up will be compared across the three groups using Chi-squared tests. Age-standardised CREDI summary scores (z-scores) analysed as continuous outcomes, reported as adjusted mean differences with 95% confidence intervalsUsing linear regression, we will assess whether breast milk CAB concentrations predict growth patterns and morbidity, adjusting for infant age, sex socio-economic status, birth weight and gestation age at birth. Random effects models will account for intra- and interindividual variability in repeated measurements. Exploring this analysis may inform algorithms for monitoring CAB safety signals in infants. These algorithms could be validated in larger studies and incorporated into routine practice for early detection of CAB-related risks in infants.	Impact of CAB breast milk exposure on infant growth and neurocognitive development in comparison to the standard daily oral PrEP.

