### Benefits of participation in the study

The direct benefit of participation in the CABMILK study is that infants would be closely monitored, and this would be particularly valuable in this sub-population, which is at higher risk of general childhood illnesses. The indirect benefit is that the study is envisaged to provide evidence on the safety of cabotegravir breast milk exposure during childhood. Although the burden of research to inform the safety of breastmilk exposure to cabotegravir is being borne by the participants in this study, the evidence will likely inform policy and practice and thereby be applied to a wider population.

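### Table 2 compares infant morbidity as event or no event per infant; an incidence rate ratio would use the repeat episodes that are already collected

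*Protocol article*

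**What the plan says.** The Discussion presents the study as an opportunity to "compare infant growth, morbidity, and early developmental milestones among infants in three exposure groups", but it does not define the morbidity outcome. The definition is in Table 2 (Data analysis, second objective): "adverse events (overall morbidity) by the end of follow-up will be compared across the three groups using Chi-squared tests".

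The Data analysis text describes safety reporting differently: "Primary safety results will be descriptive: counts, proportions with exact 95% confidence intervals, incidence rates, and Kaplan–Meier curves, without group-comparison p-values". The specific aims likewise rule out formal between-group testing.

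Step 2 states its hypothesis as no difference in the incidence of adverse events or illnesses. It plans to use the six visits to assess incidence, "with a final exit visit scheduled at eight months post initial CAB dose". On visit numbers it says: "This will result in 10 scheduled visits in the CAB group and six in the oral PrEP and no PrEP groups". Table 1 marks an adverse event assessment at every one of those scheduled visits.

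No event rate is given. The nearest statement is in the paragraph on benefits of participation: "this would be particularly valuable in this sub-population, which is at higher risk of general childhood illnesses".

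**The concern.** A chi-squared test across three groups on adverse events by the end of follow-up needs one category per infant, and the natural reading is event or no event. An infant with one mild illness and an infant with five then count the same. The number of episodes, which the repeated assessments collect, does not enter the one comparison that has a stated method.

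The descriptive list does not fully repair this. Proportions, and Kaplan–Meier curves as ordinarily drawn, use only the first event. Incidence rates could carry the repeat episodes, but the text gives no rate ratio or rate difference between groups and does not say whether repeats count. Step 2 therefore asks about incidence while Table 2 answers with a yes/no outcome.

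If CAB-exposed infants were ill more often, part of the evidence would sit in data already collected but not used in the comparison. The loss grows as more infants have at least one event.

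**Working it through.** **Inputs from the protocol.** Group sizes are 25 CAB-LA, 25 oral PrEP and 50 PrEP-naïve (Sample size section). Follow-up is 8 months. Adverse events are assessed at 10 visits in Group A and 6 in Groups B and C (Table 1, Step 2). There is no power figure, event rate or target effect for Step 2, so there is no figure of the plan's own to reproduce.

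**Assumptions, not in the protocol.** Rate in the comparator group 0.5 to 4 events per infant-year; frailty variance k from 0.25 to 1 (gamma-Poisson counts); true rate ratio 2; two-sided 5% criterion, matching 95% intervals.

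**Step 1: proportion with any event.** The expected count is μ = rate × 8/12, and P(any) = 1 − (1 + kμ)^(−1/k).
- Rate 4, k = 0.25: μ = 2.67. Comparator: 1 − 1.667^(−4) = 87%. Doubled: 1 − 2.333^(−4) = 97%.
- Rate 2, k = 1: μ = 1.33. Comparator: 1 − 1/2.33 = 57%. Doubled: 1 − 1/3.67 = 73%.
- Rate 0.5, k = 1: μ = 0.33. Comparator: 1 − 1/1.33 = 25%. Doubled: 1 − 1/1.67 = 40%.

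**Step 2: chance of flagging a doubled rate, 25 v 25** (4,000 runs per setting). Yes/no uses a chi-squared test; the rate comparison uses the log rate ratio with a robust standard error.

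| Rate per infant-year | k = 0.25: yes/no, rate | k = 0.5: yes/no, rate | k = 1: yes/no, rate |
|---|---|---|---|
| 2 | 37%, 77% | 30%, 65% | 22%, 50% |
| 3 | 31%, 87% | 27%, 75% | 20%, 56% |
| 4 | 22%, 92% | 22%, 79% | 18%, 58% |

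At 0.5 to 1 event per infant-year the ranges are 21–40% for yes/no and 28–57% for the rate. Repeat runs agree to within about 3 points. Over 0.5 to 4 events per infant-year, this gives about 17–40% for yes/no and 28–92% for the rate. With no true difference both methods flag about 4–7%, so the gain is not bought with extra false positives.

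**Step 3: would an interval on the yes/no outcome be enough?** Take 25/25 against 22/25, roughly what rate 4 and k = 0.25 would give (0.87 × 25 ≈ 22). The risk difference is 25/25 − 22/25 = 0.12, with Newcombe 95% interval −0.035 to 0.300. Dropping the p-value but keeping the outcome leaves the same loss.

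**Step 4: yes/no with no frailty.** Here p1 = 1 − (1 − p0)². Exact power of the uncorrected chi-squared test:

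| p0 | p1 | 25 v 25 | 25 v 50 |
|---|---|---|---|
| 10% | 19% | 0.15 | 0.20 |
| 40% | 64% | 0.45 | 0.54 |
| 50% | 75% | 0.48 | 0.58 |
| 70% | 91% | 0.50 | 0.57 |
| 90% | 99% | 0.19 | 0.18 |

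At low baseline risk the limit is sample size. Saturation takes over only near 90%.

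**Step 5: unequal visits.** Group A has 10 − 6 = 4 extra assessments. Suppose these inflate recorded CAB events with no true effect (2 or 4 events per infant-year, k = 0.25 to 0.5, 25 v 25). At 1.5-fold inflation the rate comparison falsely flags 28–50% of the time, against 12–17% for yes/no. At 1.2-fold the figures are 10–14% against 7–8%. A rate comparison therefore needs equal ascertainment.

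**The case against.** The strongest reply is that rates are already planned. Counts and incidence rates stand among the primary safety results, in the same sentence as the proportions, and nothing limits them to first events. A reader might infer that repeat illness is never used; the text does not support that. What stands is narrower: the only stated method for comparing the groups is the chi-squared test in Table 2, and no rate contrast is named.

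A reader might also infer that the outcome is close to its ceiling. The protocol does not show this. It gives no event rate, and its remark about childhood illness says higher risk, in a paragraph on benefits. Nor can one say that a doubled rate would usually be missed whatever the baseline: without frailty, 25 v 50 reaches 54–58% at baseline risks of 40–70%. The case for a rate does not need a ceiling, because it gained in every setting tried from 0.5 events per infant-year upward.

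The low power is openly disclosed under Sample size and Limitations, and findings are to be read cautiously. That lowers the severity but is no reason to set aside collected information.

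The analysis plan is said to be available but is not shown. Episode definitions and the choice of count model may properly be there. The yes/no comparison itself is stated in this document.

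Finally, a rate is more exposed than a yes/no outcome to the extra Group A visits. That objection stands in full, and the fix must deal with it.

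**Conclusion.** The concern holds in a limited form. Table 2's morbidity comparison most naturally reduces each infant to event or no event, does not match Step 2's question about incidence, and uses less information than a rate comparison. The size given in the working rests on assumed event rates, gamma frailty, a true doubling and 25 v 25; the gain is small when events are few and large when they are common. It also assumes equal ascertainment, which the visit schedule does not provide unless the analysis imposes it.

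The protocol does not establish saturation, and it does not claim power for safety. This is a modest improvement to a descriptive, exploratory analysis. It also removes a conflict within the document, since Table 2's chi-squared test contradicts the specific aims and the Data analysis text, which exclude between-group testing and p-values.

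**What to change.** In Table 2, replace the chi-squared test on adverse events with the all-event incidence rate ratio, repeat episodes counted, for CAB-LA versus oral PrEP and CAB-LA versus PrEP-naïve. Give 95% confidence intervals from a negative binomial or robust-variance count model with follow-up time as offset. Label the result exploratory and report no p-values, in line with the specific aims and the Data analysis text. Keep the any-event proportions and Kaplan–Meier curves as description.

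Count events for this comparison only from the six visits common to all groups (months 0, 1, 3, 5, 7 and 8), or over equal recall windows, so that the four extra Group A visits do not raise the CAB-LA rate.

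Cost: no new visits or samples. Staff need a rule that separates distinct episodes from one continuing illness. Events found only at the extra Group A visits leave the comparison but are still reported descriptively. The model adds an overdispersion or robust-variance assumption. Enrolment is ongoing, so the wording can be changed before outcomes are analysed.

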## Limitations

This study has several limitations. Enrolment from birth to five months spans a period of rapid ontogeny of Uridine Diphosphate Glucuronosyltransferase 1A1 (UGT1A1)-mediated glucuronidation and developmental change. Although population pharmacokinetic modelling incorporating maturation functions and age-standardised growth and developmental outcomes will be used, the small number of infants within age strata limits precision in characterising exposure–age relationships; findings at younger ages should therefore be interpreted with caution. Secondly, the study is not powered to detect between-group differences in infant safety, growth, or developmental outcomes, and these analyses are consequently descriptive and hypothesis-generating, with formal inference deferred to larger studies. Thirdly, infant feeding patterns and maternal nutritional status may influence infant exposure; feeding will be captured longitudinally and incorporated as a time-varying covariate, while maternal weight will be evaluated in relation to cabotegravir clearance and milk-to-plasma ratios. However, the study does not directly measure milk composition or detailed maternal dietary intake, limiting the ability to fully assess indirect dietary effects. Finally, as exposure groups are self-selected, comparative analyses are observational and exploratory, and although adjusted and sensitivity analyses will be undertaken where feasible, residual confounding cannot be excluded.

## Conclusion

Lactating women represent a key population with heightened vulnerability to HIV acquisition, and consequently, a risk of transmission to their infants. However, they remain largely underrepresented in clinical trials of novel HIV prevention agents, including long-acting cabotegravir. The CABMILK study will fill this critical evidence gap by generating foundational data on maternal, breast milk, and infant cabotegravir exposure alongside comparative assessments of infant growth and development. Findings from this study will provide early, context-specific safety data essential for informing Malawi’s national CAB-LA rollout and guiding future WHO recommendations. By strengthening the evidence base for postpartum PrEP use, this study has the potential to enhance clinical decision-making, improve community confidence in long-acting PrEP, and support equitable access to HIV prevention for lactating mothers and their infants.

## Data Availability

No participant data are associated with this article, as it describes a study protocol. Extended study materials supporting this protocol are openly available on Zenodo:
https://doi.org/10.5281/zenodo.18490313
^
24
^ These materials include the Statistical Analysis Plan, sample collection Case Report Forms (CRFs), and the laboratory analytical plan for cabotegravir quantification. Data are available under the terms of the
Creative Commons Attribution 4.0 International (CC-BY 4.0) license. De-identified individual participant data generated from the CABMILK study, including pharmacokinetic concentration data and relevant clinical and demographic variables, will be made available after study completion and publication of the primary results. Data sharing will be conducted in accordance with participant consent, Malawi national research regulations, and institutional data governance policies. Requests for access to study data will be reviewed by the study investigators and an appropriate data access committee. Data will be shared in a de-identified format, and requestors may be required to sign a data use agreement.
